**11.1.2.4. Drug interaction**

- This drug is carefully administered to patients who are receiving  $\beta$ -adrenaline antagonists due to the possibility of cardiac conduction disorders.
- If the drug having parasympathetic nerve excitement is administered at the same time as this drug, an agonizing effect is expected. The simultaneous use of this drug and anticholinergic drugs (atropine, inhalation ipratropinium) antagonizes the effect.
- Although no typical drug interaction experiment was performed, the following drugs were co-administered to at least 10% of patients with Sjogren's syndrome.
- Acetylsalicylic acid, artificial tears, calcium, coupled estrogen, hydroxychloroquine sulfate, ibuprofen, levothyroxine sodium salt, acetic levothyroxine, Medroxyprogesterone acetate, methotrexate, naphroxene, omeprazole, paracetamol, prednisone

**11.1.2.5. Administration to pregnant women**

- When 90 mg/kg per day (26 times the maximum amount per adult) was orally administered in pregnant female rats, it was associated with a decrease in average gestational body weight and an increase in skeletal changes. When 36 mg/kg per day (10 times the maximum amount per adult) was orally administered during pregnancy and lactation, the mortality rate increased, and administration of dosages more than 18 mg/kg per day (5 times the maximum amount per adult) was associated with a decrease in the survival and the average body weight of newborn babies. There is no proper and well-planned clinical trial on pregnant women, thus when administered during pregnancy, it should be used only when the benefits exceed the risk to the fetus

**11.1.2.6. Administration to lactating women**

- It is not known whether this drug is secreted from breast milk. However, since many drugs are transferred and secreted to breast milk, and have the potential to cause a series of adverse reactions to infants during lactation, it is necessary to stop breastfeeding or consider discontinuation of medication in consideration of the benefits of this drug to the mother.

**11.1.2.7. Administration to children**

- Safety and efficacy in children have not been demonstrated.

**11.1.2.8. Administration for the elderly**

- 1) Patients with head and neck cancer: In a trial of 15 elderly volunteers, five women exhibited a higher maximum blood concentration and lower area under the curve (AUC) compared to 10 men

Version 2.6

- 2) When administered to elderly patients with Sjogren's syndrome, there has been a report of an increase in frequent urination, diarrhea, and dizziness.

#### **11.1.3. Treatment when overdosing**

- This drug is considered to have a fatal potential when administered more than 100mg. Treatment for overdose should be administered subcutaneously or intravenously with atropine (0.5mg to 1.0mg), and the maintenance of breathing and circulation effective for maintaining the patient's physical strength should be adjusted. In addition, when there is severe cardiovascular function decline or bronchoconstriction, it is desirable to subcutaneously or intravenously administer epinephrine (0.3mg to 1.0mg). It is not known whether this drug is dialyzable.

#### **11.1.4. Others**

- 1) In the case of oral administration of this drug to patients with renal and liver diseases, the pharmacology for this is unknown.
- 2) Carcinogenesis: Oral carcinogenesis studies at survival state were conducted in CD-1 mice and SD rats. The drug did not cause cancer in mice at any dose trial (dose administered approximately 50 times more than the maximum systemic dose clinically observed, up to 30 mg/kg/day). In rats, there was a statistically significant increase in the expression of benign pheochromocytoma in males and females and in the expression of hepatocellular adenoma in female rats at a dose of approximately 100 times more than the maximum systemic dose observed clinically. The carcinogenesis observed in rats was seen only in several batches of the maximum clinical allowance and does not appear to be associated with clinical use.
- 3) Mutagenesis: No evidence has been obtained from the following studies that the drug

## Version 2.6

can cause genotoxicity.

- ① Assessment of Bacteria for Reverse gene mutation (Salmonella and E. coli)
- ② Evaluation of in vitro chromosomal mutation in Chinese hamster ovarian cell line
- ③ Evaluate of in vivo chromosome mutation in mice (micronucleus)
- ④ Evaluation of primary DNA damage in rat hepatocyte culture (non-scheduled DNA synthesis)
- 4) Impaired fertility: The drug was orally administered to male and female rats at an 18 mg/kg/day dose (a dose approximately 100 times more than the maximum systemic dose observed clinically) indicating impaired fertility, including decreased fertility, decreased sperm motility, and morphological evidence of abnormal spermatozoa. It is unclear whether the decrease in fertility is an effect on male or female animals, or both. When dogs were given the main agent at a 3 mg/kg/day dose for 6 months (about three times the maximum adult dose), the results of impaired sperm bioactivity were shown. This result indicates that the drug may damage the fertility of men and women.
- People planning to become pregnant should be administered only when the benefits of this drug exceed fertility impairment

#### **11.1.5.Storage and handling precautions**

- 1) Keep it out of reach of children.
- 2) Be careful because replacing it in another container can cause an accident or it is not desirable in terms of quality maintenance.

### **11.2. Baekhogainsam-Tang**

#### **11.2.1.Predictive side effects**

- (1) Skin: rash, urticaria, etc

## Version 2.6

- (2) Digestive system: loss of appetite, stomach irritation, watery stool, diarrhea, etc
- (3) Pseudo-aldosteronism: Decreased urine volume, swollen face, hands and feet, heavy eyelids, stiffened hands, high blood pressure, headache, etc. (If a medicine with a maximum dose of 1g or more as licorice is taken for a long period of time, it may cause pseudo-aldosteronism such as hypokalemia, elevated blood pressure, retention of sodium fluid, swelling, and weight gain, thus observe (measure the serum potassium level) sufficiently and stop taking it if abnormalities are found.)
- (4) Myopathy: Since myopathy may appear as a result of hypokalemia, make sufficient observation and stop taking it if abnormalities such as weakness, quadriceps cramps, paralysis, etc. are identified.

**11.2.2. Precautions**

- (1) The following persons shall consult with their doctors, oriental doctors, dentists, pharmacists and oriental pharmacists before taking this medicine.
- 1) HTN patients
- 2) Patients with cardiac arrest or renal impairment
- 3) Patients with swelling
- 4) Patients with weak stomachs and coldness (deprived appetite, stomach discomfort, watery stools, diarrhea, etc. can occur)
- 5) Weak patients with / without weakened physical strength (adverse reactions can easily occur and symptoms can worsen)
- 6) Pregnant woman or likely pregnant woman
- 7) Patients being treated by a doctor (who are being given other drugs)
- 8) Elderly people (In general, elderly people have a decreased physiological function, thus be careful, such as reducing the dose of the drug)

## Version 2.6

- 9) Children (no safety is established for children (less experience in use))
  
- (2) Other precautions to be taken when taking this drug
- 1) Adherence to the specified usage and capacity
- 2) In principle, it is not to take it continuously for a long time, but if it is unavoidable to take it continuously for a long time, consult with doctors, oriental doctors, dentists, pharmacists, and oriental pharmacists.
- 3) When combined with potassium-containing preparations, licorice-containing preparations, glycyric acid-containing preparations, loop diuretics (furosemide, etacrine) or thiazide diuretics (trichloromethiazide), myopathy is likely to occur due to pseudo-aldosteronism or hypokalemia, so take it carefully.
- 4) When taken with other herbal medicines, etc., be careful about overlapping containing herbal medicines.
  
- (3) Precautions for Storage
- 1) Avoid direct sunlight and store it in a cool place with as little moisture as possible (must keep it sealed after use).
- 2) Keep it out of reach of children.
- 3) Take the medicine out of the original container and store it in another container, which may cause an accident or deterioration in the quality of the medicine due to misuse, thus put it in the original container and keep it tightly closed.

## 12. Suspension and withdrawal criteria

### 12.1. Suspension and withdrawal criteria

## Version 2.6

- If the conditions to be excluded from the selection of test subjects are determined after screening
- If the test subject or guardian withdraws consent to participate in the clinical trial
- In the event that a serious violation of the clinical trial plan, such as the criteria for inclusion and exclusion, is discovered during the clinical trial
- In the event of a serious adverse events/drug reaction
- When the test subject has administered the drug that is expected to affect the evaluation of the safety and effectiveness of a clinical trial drug
- In case of taking a combination-prohibited drug during a clinical trial
- In the event that the progress of clinical studies is deemed inappropriate by the judgement of the principal investigator or sub-investigator

**12.2. Management in case of suspension and withdrawal**

- If the test subject is suspended or withdrawn, the administration of the trial drug shall be stopped, and all data obtained up to the time of suspension and withdrawal shall be recorded in the electronic case report form (e-CRF) along with the date of suspension (final administration), reasons for suspension or withdrawn, and treatment and progress at suspension or withdrawn.

**12.3. Management of violation of clinical trial plan**

- The investigator must be fully aware of and thoroughly implement the clinical trial plan to prevent violations of that.
- In the event of a serious violation of the clinical trial plan, the test subject should be withdrawn from the analysis (excluding per-protocol analysis), and the relevant cases are as follows.

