| Statistical methods | 
1. Patients group for data analysis
 
 
- Demographic information will be assessed for all participants.
 
- Safety outcomes will be analyzed in the intention-to-treat (ITT) population.
 
- Efficacy outcomes will be analyzed for both the per-protocol (PP) and ITT populations. In case of discrepancies between the efficacy outcomes of PP and ITT populations, both set of results will be presented and compared, with the PP population considered the main analysis and the ITT population as supplementary analysis.
 
- The ITT population consists of participants who received at least one dose of the clinical trial drugs and underwent efficacy evaluation more than once during the treatment period. In cases of missing values due to dropouts or discontinuation before the clinical trial ends, missing data from dropout participants will be imputed using the last observation carried forward analysis.
 
- The PP population is a subset of the ITT population. It includes participants who consumed >70% of the prescribed doses of clinical study drugs and completed follow-up visits and corresponding outcome measurements (weeks 4, 8, and 12) during the 12-weeks treatment periods. Participants falling under a 'significant violation of clinical trial plan' will be excluded
 
 |

from the PP population.

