## Version 2.6

- 1) No written informed consent obtained
  - 2) Violation of inclusion and exclusion criteria
  - 3) If a prohibited drug is administered during the clinical trial period
  - 4) If the main examination at the start and end of the clinical trial is missing
  - 5) If the clinical trial drug's compliance is less than 70%
- Medication compliance (%) is defined by dividing the actually consumed tablets by the total numbers of tablets prescribed during the clinical trial period, and if this value is less than 70%, it is withdrawn.
  - Other minor violations of the clinical trial plan that are not considered to affect the interpretation of research results are included in the per-protocol analysis by clearly stating the degree and reason for the violation or delay, and comprehensively considering whether the violation or delay affected the clinical trial.

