##### **13.1.3. Efficacy outcomes**

- Efficacy outcomes will be analyzed for both the per-protocol (PP) and ITT populations. In case of discrepancies between the efficacy outcomes of PP and ITT populations, both set of results will be presented and compared, with the PP population considered the main

Version 2.6

analysis and the ITT population as supplementary analysis.

- The ITT population consists of participants who received at least one dose of the clinical trial drugs and underwent efficacy evaluation more than once during the treatment period. In cases of missing values due to dropouts or discontinuation before the clinical trial ends, missing data from dropout participants will be imputed using the last observation carried forward analysis.
- The PP population is a subset of the ITT population. It includes participants who consumed >70% of the prescribed doses of clinical study drugs and completed follow-up visits and corresponding outcome measurements (weeks 4, 8, and 12) during the 12-weeks treatment periods. Participants falling under a 'significant violation of clinical trial plan' will be excluded from the PP population.

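### Section 12.3, read literally, takes serious violators out of ITT and keeps them in per-protocol, the reverse of section 13.1.3; probably a slip, but it governs who is analysed for efficacy and safety

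*Protocol*

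**What the plan says.** Section 12.3 sets the consequence of a serious violation: "the test subject should be withdrawn from the analysis (excluding per-protocol analysis"). It then lists five such violations: no written consent, breach of the eligibility criteria, use of a prohibited drug, a missing main examination, and compliance below 70%. The same section adds: "Other minor violations of the clinical trial plan that are not considered to affect the interpretation of research results are included in the per-protocol analysis", subject to documentation and review.

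Section 13.1.3, repeated in the synopsis, defines the analysis sets. ITT is described as follows: "The ITT population consists of participants who received at least one dose of the clinical trial drugs and underwent efficacy evaluation more than once" during treatment. It carries no exclusion for violations, and last observation carried forward is specified for dropouts. For PP it says "The PP population is a subset of the ITT population" and requires more than 70% of doses and complete visits at weeks 4, 8 and 12. It adds: "Participants falling under a 'significant violation of clinical trial plan' will be excluded from the PP population".

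If the two efficacy results differ, both are presented and compared, "with the PP population considered the main analysis and the ITT population as supplementary analysis". Sections 13.1.2 and 13.4 place the safety analysis in the ITT population.

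**The concern.** The exception in 12.3 names the wrong analysis. A programmer who builds the sets from 13.1.3 finds no list of what counts as a significant violation and has to go to 12.3 for it, where the instruction attached to the list is reversed.

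Three things are at stake. First, PP is the main analysis when the sets differ, and the literal rule would put into it people who took prohibited drugs or less than 70% of their tablets. Second, ITT would lose non-adherent participants, including dropouts whose values 13.1.3 says to impute. Third, because safety is analysed in ITT, people who stopped their tablets because of side effects could drop out of the safety comparison. Fewer side effects is half of the objective in section 4.1, and section 11.1.1 names sweating as the most frequent reason for stopping pilocarpine in Sjogren's syndrome. Adherence may therefore differ by arm, and an exclusion based on it may not be balanced.

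**Working it through.** This is a question of wording, so the check is to set the rules side by side.

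| Question | 12.3, read literally | 13.1.3 and synopsis |
|---|---|---|
| Serious violator in PP? | Yes, PP is the exception | No, excluded |
| Serious violator in ITT? | No, withdrawn | Yes, if dosed and evaluated as defined |
| Serious violator in safety (= ITT)? | No | Yes, on the same condition |
| Term used | serious | significant |
| Compliance boundary | below 70% is a violation | above 70% is needed for PP |

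1. *Can the literal rule be carried out?* No. PP is a subset of ITT, so anyone removed from ITT is removed from PP as well. *Out of ITT, kept in PP* describes an empty set.

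2. *Which reading is meant?* 12.3 lets minor violations into PP, which makes sense only if serious ones are kept out. With the explicit exclusion in 13.1.3 and the synopsis, this points to a slip for exclusion from the per-protocol analysis.

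3. *Does a milder reading remove the conflict?* No. If 12.3 is taken to mean withdrawal from analysis in general, it still contradicts the ITT definition, which has no violation-based exclusion. The compliance bullet in 12.3 also says that a participant below 70% is withdrawn, without saying from which set.

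4. *Boundary.* Compliance of exactly 70% is not a violation under 12.3 and does not qualify for PP under 13.1.3.

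5. *Size.* The planned sample size reproduces. With one-sided alpha 0.05, power 90%, SD 0.35, margin 0.21 and true difference 0 (section 8.4), n per arm = 2 × [0.35 × (1.645 + 1.282) / 0.21]² = 47.6, so 48; 48 / 0.80 = 60 per arm, 120 in total. The protocol gives a 20% dropout allowance but no expected number of serious violators, so the number of participants affected cannot be derived.

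6. *Side calculation, for the optional advice under fix.* Suppose non-inferiority had to be shown in both sets. Inputs: 48 per arm in PP and 60 in ITT, SD 0.35, margin 0.21, and the two-sided 95% interval of section 13.3.1.2 (z = 1.96). Standard error = 0.35 × √(2/n): 0.0714 for PP and 0.0639 for ITT. Correlation of the two estimates = √(48/60) = 0.894. Power = Φ[(0.21 − deficit)/SE − 1.96]; the joint figure is bivariate normal.

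| True deficit (mL/min) | PP alone | Both | Cost of requiring both |
|---|---|---|---|
| 0 | 83.6% | 82.4% | 1.2 points |
| 0.105 | 31.2% | 27.1% | 4.1 points |

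This treats the 20% dropout as the PP exclusion, gives both sets the same mean and SD, and ignores carried-forward values and selection. It prices the stricter rule and does not measure the harm from the contradiction.

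**The case against.** The best defence is that the document corrects itself. The section devoted to analysis sets is clear, the synopsis repeats it, the minor-violation sentence in 12.3 agrees with it, and the literal rule is impossible. On that view one parenthesis was mistranslated and nobody would follow it. What stands is that the intended reading is recoverable, and that there is no sign of a plan to keep violators only in PP. What does not stand is that this makes the sentence harmless: 12.3 is where the violations are listed, and the milder reading still conflicts with the ITT and safety sets.

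A reader might go further in three ways, none supported by the text.

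- *That PP alone decides when the sets disagree.* The protocol has both results presented and compared, with PP main and ITT supplementary. Naming a main set in advance is a stated choice. Requiring both sets to pass is a stricter design preference.
- *That the visit rules contradict each other.* 12.3 lists as a violation "If the main examination at the start and end of the clinical trial is missing", while 13.1.3 asks for weeks 4, 8 and 12. These conditions are cumulative and can be applied together.
- *That the 20% dropout allowance gives the number of violators.* Dropouts and violators are different groups: a completer can take a prohibited drug or fall below 70% compliance.

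**Conclusion.** The contradiction is real and sits in an operative rule. 12.3 as worded reverses 13.1.3 and the synopsis and is incompatible with PP being a subset of ITT. It is most likely a wording slip, and should be corrected before the analysis sets are fixed, because membership of the main efficacy set, the ITT efficacy set and the safety set turns on it. Its numerical effect is unknown, because the protocol states no expected violation rate. The conclusion rests on the text of the two sections alone and on no power calculation. The difference of term and the gap at exactly 70% compliance are smaller inconsistencies in the same rule.

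**What to change.** Reword the sentence in 12.3, for example:

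> Serious violators are excluded from the per-protocol analysis only. Those who meet the ITT definition in 13.1.3 stay in the ITT and safety analyses in the arm to which they were randomised, except participants without written informed consent.

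The consent exception is needed because lack of consent is the first violation on the list, and such data should not be kept in ITT by default. Limiting the rule to those who meet the ITT definition avoids a new conflict with 13.1.3.

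Use one term, *serious* or *significant*, in both sections, let 13.1.3 refer to the list in 12.3, and state the 70% boundary for PP the same way in both, so that exactly 70% falls on one side. The compliance bullet in 12.3 should say which set it refers to. The cost is a few words of protocol text, with no effect on sample size or power.

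Optional: state that non-inferiority is concluded only if it is shown in both PP and ITT. Under the assumptions above this costs about 1 point of power at a true difference of 0 and about 4 points at a deficit of 0.105. The correction to 12.3 does not depend on it.

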## Version 2.6

- 1) No written informed consent obtained
  - 2) Violation of inclusion and exclusion criteria
  - 3) If a prohibited drug is administered during the clinical trial period
  - 4) If the main examination at the start and end of the clinical trial is missing
  - 5) If the clinical trial drug's compliance is less than 70%
- Medication compliance (%) is defined by dividing the actually consumed tablets by the total numbers of tablets prescribed during the clinical trial period, and if this value is less than 70%, it is withdrawn.
  - Other minor violations of the clinical trial plan that are not considered to affect the interpretation of research results are included in the per-protocol analysis by clearly stating the degree and reason for the violation or delay, and comprehensively considering whether the violation or delay affected the clinical trial.

### **13. Evaluation criteria, methods, and statistical analysis**

#### **13.1. Patient group for data analysis**

##### **13.1.1. Demographic information**

- Demographic information will be assessed for all participants.

##### **13.1.2. Safety outcomes**

- Safety outcomes will be analyzed in the intention-to-treat (ITT) population.
- The original data are analyzed without correction of the data.

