## **4. The objective and background of the study**

### **4.1. Objective**

- To ascertain whether combined administration of BIT herbal medicine and low-dose pilocarpine can demonstrate both non-inferior efficacy and fewer side effects in patients with frequent intractable xerostomia (patients who underwent radiation therapy to the head and neck or with Sjogren's syndrome) than the administration of only high-dose pilocarpine.

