## **10.2. Evaluation of efficacy**

### **10.2.1. Salivary flow rate (SFR) test**

- Visit 2 (Week 0) is replaced by screening test.
- Evaluation at Visit 3 (Week 4), Visit 4 (Week 8), Visit 5 (Week 12).

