#### **13.4.1.1. Adverse events (AE)**

- Adverse events (AEs) are standardized into system organ class (SOC) and preferred term (PT) based on MedDRA ver. 23.1 (Korean).
- For AEs and drug reactions in this clinical trial, the frequency (number of test subjects), percentage, and number of occurrences are presented based on SOC and PT for each group.
- For serious AEs, the frequency, percentage, and number of occurrences are presented based on SOC for each group. Serious AEs are also summarized in a list of AEs, periods, courses, severity, outcomes, and causal relationships.
- In addition, individual lists of all test subjects with AEs are presented (including experimental/control group, reported AEs, start date/time and end date/time, course, intensity, seriousness, the association with clinical trial drugs, action taken, and final outcomes). AEs that caused discontinuation of the test are presented as a separate list. AEs are summarized using the preferred terms according to MedDRA ver. 23.1 (Korean).

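### Adverse-event rates are computed in an ITT set that requires efficacy evaluations, so treated participants who stop early can drop out of the rates

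*Protocol*

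**What the plan says.** The objective in Protocol 4.1 has two parts: to find out whether the combination "can demonstrate both non-inferior efficacy and fewer side effects" compared with high-dose pilocarpine alone.

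The safety population is fixed in 13.1.2: "Safety outcomes will be analyzed in the intention-to-treat (ITT) population". Section 13.4 and the Statistical methods row of the protocol summary repeat this, and no separate all-treated set is defined. Section 13.1.3 restricts the ITT set to those who "received at least one dose of the clinical trial drugs and underwent efficacy evaluation more than once during the treatment period".

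Adverse events are tabulated by arm. Section 13.4.1.1 says that "the frequency (number of test subjects), percentage, and number of occurrences are presented based on SOC and PT for each group". The same section adds that "individual lists of all test subjects with AEs are presented", with a separate list of events that led to discontinuation.

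**The concern.** Whether a treated participant counts in the side-effect rates depends on staying long enough to have efficacy measured. That condition is tied to the outcome. Section 11.1.1 reports sweating as the commonest reason why patients with Sjogren's syndrome stopped pilocarpine, and 12.1 makes a serious adverse event or drug reaction a ground for suspension or withdrawal. A participant withdrawn in week 2 for such an event would be missing from the frequency tables meant to count it.

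The trial's own hypothesis (4.4) is that side effects are commoner on full-dose pilocarpine. Removal from the rates may therefore differ between arms and distort the contrast that the second half of the objective is about. It could also hide early intolerance of the herbal product. Because the listings are not restricted in the same way, the tables and the listings can disagree about who had an event.

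**Working it through.** **Who is excluded.** SFR and VAS are measured on treatment at weeks 4, 8 and 12, and the week 0 value is taken from screening (10.2.1, 10.2.2). OHIP-14 and scintigraphy are also efficacy evaluations and are done at Visit 2, week 0 (10.2.3, 10.2.4). The schedule in 9.2 places Visit 2 under the treatment period, although 9.9.2 describes it as before administration. Counting evaluation occasions rather than instruments, there are four readings:

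| | More than one evaluation needed | At least one was meant |
|---|---|---|
| Only post-dose evaluations count | must reach week 8 | must reach week 4 |
| Visit 2 also counts | must reach week 4 | nobody lost who was evaluated at Visit 2 and then dosed |

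Three of the four readings lose at least everyone who stops before week 4.

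**The plan's own figure.** The protocol gives no adverse-event rate. Its only sizing (8.4) is for SFR: σ = 0.35, margin 0.21, one-sided α = 0.05, power 90%.

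n = 2 × 0.35² × (1.645 + 1.282)² / 0.21² = 47.6, rounded up to 48 per arm; 48 / 0.80 = 60.

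Both figures reproduce. They say nothing about precision for side effects.

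**Size of the bias (illustration).** Inputs: 60 per arm (8.3). Event rates of 50% control and 30% experimental are assumed, that is 30/60 and 18/60, a difference of 20.0 points. Everyone excluded is assumed to have had an event. With k excluded from an arm with x events among n, the tabulated rate is (x − k)/(n − k).

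| Excluded, control v experimental | Control | Experimental | Difference (points) |
|---|---|---|---|
| 0 v 0 | 30/60 = 50.0% | 18/60 = 30.0% | 20.0 |
| 3 v 0 | 27/57 = 47.4% | 30.0% | 17.4 |
| 6 v 0 | 24/54 = 44.4% | 30.0% | 14.4 |
| 9 v 0 | 21/51 = 41.2% | 30.0% | 11.2 |
| 12 v 0 | 18/48 = 37.5% | 30.0% | 7.5 |
| 9 v 3 | 41.2% | 15/57 = 26.3% | 14.9 |
| 6 v 3 | 44.4% | 26.3% | 18.1 |
| 4 v 3 | 26/56 = 46.4% | 26.3% | 20.1 |
| 3 v 3 | 47.4% | 26.3% | 21.1 |

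The rate falls by k(n − x)/[n(n − k)]. Three exclusions therefore cost the control arm 3 × 30/(60 × 57) = 2.6 points and the experimental arm 3 × 42/(60 × 57) = 3.7 points. This is why equal counts widen the difference slightly, and why the control excess must be more than trivial before it shrinks.

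Twelve is the whole 20% dropout allowance for one arm (0.20 × 60), so the 12 v 0 row is an extreme.

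**Precision with everyone included.** At 50% v 30% and 60 per arm, the 95% CI half-width for the risk difference is 1.96 × √[(0.25 + 0.21)/60] = 0.172, about 17 points. Power for a two-sided 5% comparison is about 61%.

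**The case against.** - **Early stoppers are not lost altogether.** A reader might infer that they vanish. The documents do not support that: 13.4.1.1 lists every participant with an adverse event and, separately, events that caused discontinuation; 13.4 has all participants' vital signs, examinations and laboratory results charted; and 12.2 records data up to withdrawal. This objection stands. The loss is from the rates only.
- **The week 8 cut-off is one reading.** Counting the Visit 2 assessments, as the schedule heading permits, moves it to week 4. If at least one evaluation was also meant, nobody evaluated at Visit 2 and then dosed is lost. This stands too, but it takes two departures from the natural sense of the text to remove the problem.
- **Safety is compared in some form.** A reader might infer that the arms are never compared, so that fewer side effects could not be concluded at all. That goes too far. Event percentages are given by arm, the Trial design row of the summary states an aim to compare safety, and 14.5 allows testing of laboratory values. An SAP that is not shown may hold the method. What can fairly be said is that the protocol itself names no side-effect endpoint for this part of its objective.
- **The direction may be conservative.** If exclusions are mostly in the control arm, the difference shrinks, which works against the sponsor's claim. This holds under that assumption, but the direction is not guaranteed, and a set that can understate early intolerance in either arm is a poor basis for safety rates.

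**Conclusion.** The population rule is wrong as written. Adverse-event rates should not depend on having had efficacy evaluations, and on every reading but the most lenient one the rule removes treated participants who stop before week 4 or week 8.

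The size cannot be fixed from the documents, because they give neither event rates nor early-stopping rates. Under the assumed 50% v 30%, the tabulated difference runs from 7.5 to 21.1 points across the scenarios against a true 20. It depends on how unequal the exclusions are: 6 v 3 changes little, 9 v 3 costs about 5 points (20.0 − 14.9 = 5.1), and 3 v 3 adds about 1. A smaller difference is the likelier direction only if early exclusions are clearly commoner on full-dose pilocarpine, which is plausible but not shown. The finding concerns the rates and their agreement with the listings; it does not show that early events go unrecorded.

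**What to change.** In 13.1.2, 13.4 and the Statistical methods row of the summary, define a safety set of all participants who received at least one dose of trial drug, with no efficacy-evaluation condition, and use it for every adverse-event table. Tables and listings will then cover the same people.

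Since fewer side effects is part of the objective, also report the proportion with at least one adverse event in each arm, with the risk difference and its 95% CI. This should be labelled a supportive estimate and not a second criterion for success. With about 61% power at 50% v 30%, requiring it as well as the SFR criterion would cut joint power to about 0.90 × 0.61 = 0.55 if the two were independent, and the event reports come from an open-label trial.

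The cost is a wording change and one extra table. The data are already required up to withdrawal under 12.2. The interval will be wide, about ±17 points under the assumed rates.
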